## Abstract

**Background:** In a disease that has only existed for 18 months, it is difficult to be fully informed of the long-term sequelae of severe acute respiratory syndrome coronavirus-2 (SARS-CoV-2) infection. Evidence is growing that most organ systems can be affected by the virus, causing severe disabilities in survivors. The extent of the aftermath will declare itself over the next 5–10 years, but it is likely to be substantial with profound socio-economic impact on society.

**Methods:** This is an international multi-center, prospective long-term follow-up study of patients who developed severe coronavirus disease-2019 (COVID-19) and were admitted to Intensive Care Units (ICUs). The study will be conducted at international tertiary hospitals. Patients will be monitored from time of ICU discharge up to 24 months. Information will be collected on demographics, co-existing illnesses before ICU admission, severity of illness during ICU admission and post-ICU quality of life as well as organ dysfunction and recovery. Statistical analysis will consist of patient trajectories over time for the key variables of quality of life and organ function. Using latent class analysis, we will determine if there are distinct patterns of patients in terms of recovery. Multivariable regression analyses will be used to examine associations between baseline characteristics and severity variables upon admission and discharge in the ICU, and how these impact outcomes at all follow-up time points up to 2 years.

**Ethics and Dissemination:** The core study team and local principal investigators will ensure that the study adheres to all relevant national and local regulations, and that the necessary approvals are in place before a site may enroll patients.

**Clinical Trial Registration:**anzctr.org.au: ACTRN12620000799954.

## Strengths and Limitations of This Study

- This is a comprehensive international long-term (2 years) follow-up study in COVID-19 ICU survivors.- Multi organ assessment of injury and recovery due to SARS-CoV-2 will be investigated.- Results will potentially assist clinicians in the management of long-term COVID-19 following severe disease by defining high risk groups for follow-up and guiding personalized rehabilitation.- Quality of recorded data will depend on physicians and research staff and in the case of high clinical workload, data completeness and accuracy could be limited.

## Introduction

A large proportion of the worldwide population has been infected by severe acute respiratory syndrome coronavirus 2 (SARS-CoV-2) during the 2020 pandemic. Whilst the vast majority of patients have survived the acute illness with minimal sequelae (1), a subgroup may suffer serious long-term sequelae (2–5), commonly referred to as “long COVID,” potentially creating a new burden to public health systems worldwide (6).

Evidence from previous investigations of the 2003 Severe Acute Respiratory Syndrome (SARS) outbreak indicates that coronaviruses substantially affect the long-term quality of life and pulmonary function in survivors. Indeed, up to one third of SARS patients had persistent pulmonary abnormalities in lung function (7, 8) and chest x-ray (9), even after 1 year from Intensive Care Unit (ICU) discharge, as well as impaired quality of life (9). Preliminary data show that at least 10% of all hospitalized COVID-19 survivors have been readmitted within 2 months (10) and presented a 33% increase in risk of developing new psychiatric or neurological diseases within the first 3 months (11, 12).

During the ongoing pandemic, up to 10 to 20% of hospitalized COVID-19 patients required admission to ICUs (1, 13), with over half of these patients requiring intubation and invasive mechanical ventilation mainly due to ARDS (1). It is well established from the literature that critical care illnesses, such as sepsis or acute respiratory distress syndrome (ARDS), are risk factors for long-term physical and neurological impairment (14–18). Similarly, COVID-19 patients in the ICU often present with severe septic shock and ARDS, ultimately requiring long-term mechanical ventilation. Thus, a large range of debilitating sequelae in those critically ill COVID-19 patients is expected (4, 19).

In response to the COVID-19 pandemic, the *COVID-19 Critical Care Consortium Observational Study* (CCCC; www.covid-critical.com) (20) was developed, an international observational cohort study, with the aim to characterize risk factors, clinical features, and outcomes of the sickest COVID-19 patients admitted to ICUs. As of May 2021, the CCCC includes 370 sites across 53 countries and has included over 10‘000 patients globally. Thus, through the COVID-19 CCC network, we aim to determine international prevalence and outcomes of patients with long-term COVID-19 to elucidate the pathophysiology of organ injury and recovery.

### Eligibility

Patients qualified for enrolment if the following conditions were fulfilled: 1) laboratory-confirmed SARS-CoV-2 infection by real-time polymerase chain reaction and/or next generation sequencing 2) written informed consent from the patient at the time of discharge from the hospital or first follow-up 3) age ≥18 years 4) ICU admission diagnosis of COVID-19 infection and/or any of its related complications, i.e., respiratory failure, sepsis and septic shock, acute liver, kidney or cardiac injury, secondary infection, rhabdomyolysis, coagulation disorders or disseminated intravascular coagulation. Previous enrolment into the CCCC observational study is favorable but not mandatory. Exclusion criteria are 1) pregnancy at time of infection 2) inability to complete long-term follow-up, due to logistical problems 3) paralysis due to pre-existing neurological condition before being admitted to hospital for COVID-19 4) history of pulmonary resection 5) previous pulmonary transplant 6) documented advanced neurologic disorder which precludes 6-min walking test 7) documented psychiatric disease for which the patient is unable to carry out the interviews.

### Screening and Recruitment

Suitable patients within the AFTERCOR network will be identified by study personnel and approached for written informed consent while in recovery after ICU discharge or at the first scheduled follow-up assessment. Informed consent will be obtained directly from the patient.

### Enrolment and Participating Sites

Study enrolment began on January 1st 2021. Currently, 14 centers in 11 countries (Italy, Spain, Ireland, Austria, United States, Australia, South Africa, Japan, Argentina, Brazil, Colombia) are participating whilst more sites are being recruited. Co-enrolment in other studies is possible as long as these are observational only.

### Outcome Measures

Follow-up assessments will be scheduled as outpatient clinic visits at 3, 6, 12, 18, and 24 months post-hospital discharge (Table 1).

**Table 1 T1:** Planned assessments per follow-up time point.

	**3 months**	**6 months**	**12 months**	**18 months**	**24 months**
Frailty score	x				
**Quality of life, psychiatric symptoms**					
SF-36	x	x	x	x	x
PHQ-9	x	x	x	x	x
**Pulmonary assessment**					
SGRQ	x	x	x	x	x
Spirometry^†^	x	x	x	x	x
aBGA^†^	x	x	x	x	x
Body phletysmography^†^	x	x	x	x	x
Airway resistance^†^	x	x	x	x	x
6-min WT^†^	x	x	x	x	x
Chest x-ray^†^	x	x	x		x
CT^*^		x			
MoCA	x	x	x	x	x
Blood analysis	x	x	x	x	x
Echocardiography^*^	x		x		x

*SF-36, Short Form Health Survey 36; SGRQ, St George Respiratory Questionnaire; PHQ-9, Patient Health Questionnaire-9; aBGA, arterial blood gas analysis; WT, walking test; MoCA, Montreal cognitive Assessment*.

† *Assessments will be repeated upon normalization*.

* *Only if CT and/or echocardiography was undertaken while on ICU*.

#### Pulmonary Assessment

Any admission for respiratory failure or a new respiratory infection since ICU discharge or last follow-up visit will be recorded. The St. George's respiratory questionnaire will be used to measure the subjective self-reported quality of life associated with chronic respiratory diseases (7, 21). Basic spirometry pre- and post-bronchodilation according to the standards of the American Thoracic Society (22) will be performed at every follow-up visit or until normalization. If in the subsequent arterial blood gas analysis, the partial pressures of oxygen and carbon dioxide are <75 mmHg or >42 mmHg, respectively by breathing room air, we will extend assessments by body plethysmography, measurement of airway resistance and gas exchange.

A standardized 6-minute walking test will be carried out following recommendations from the European Respiratory Society (23). A conventional chest x-ray will be performed and additionally, in patients who underwent a chest computer tomography scan during their ICU stay, a follow-up computer tomography scan will be done at 6 months to assess persisting changes.

Pulmonary function tests, arterial blood gas analysis, chest x-ray and the 6-minute walking test will be performed at every follow-up visit or until normalization of the test results. If a result is deemed to be in the normal range for the patient, the test will not be repeated during the following visits.

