### Statistical Considerations

Summary statistics will be used to describe the sample characteristics at ICU discharge and plots to summarize outcomes over time for both individual patients and averages by groups. Patient trajectories will be plotted over time following discharge to examine patterns in recovery for the key variables of quality of life and lung health. Mean trajectories will be used to summarize the typical trajectory. Latent class analysis will be used to determine whether there are distinct groups of patients in terms of recovery, e.g., fast and slow recovery groups, and whether these groups have particular clinical characteristics. Multivariable regression analyses will be used to examine associations between baseline characteristics and severity variables upon admission and discharge in the ICU, and how these impact outcomes at 3, 6, 12, 18, and 24 months after ICU discharge. The residuals of the models will be checked for multi-modality, skew and outliers. Models will also be checked for collinearity and influential values. Participant drop-out rates will be displayed over time and we will examine whether patient characteristics at baseline predict drop-out. Item-missing data will be summarized, and we may use multiple imputation methods as a sensitivity analysis to compensate for missing data. Long-term survival will be plotted using a Kaplan–Meier plot with censoring for patients lost to follow-up. A multivariable survival model will be used to examine which variables predict survival. We will use the lasso to select the important subset of predictors from a larger set. All analysis will be performed with R (R Foundation for Statistical Computing, Vienna, Austria).

The results of this study will be reported as according to the STROBE guidelines (29).

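### Lung tests stop after a normal result, so means or regressions of recorded values from 6 months on would understate recovery; the Table 1 footnote contradicts the stopping rule

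*Protocol article*

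**What the plan says.** Pulmonary Assessment states the rule twice. The four kinds of test "will be performed at every follow-up visit or until normalization of the test results", and then: "If a result is deemed to be in the normal range for the patient, the test will not be repeated during the following visits". No limit for normal is given in the article.

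Table 1 puts a dagger on spirometry, arterial blood gas, body plethysmography, airway resistance, the 6-minute walk and chest x-ray. The footnote to that dagger reads: "Assessments will be repeated upon normalization".

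Follow-up consists of "outpatient clinic visits at 3, 6, 12, 18, and 24 months post-hospital discharge".

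Statistical Considerations plots patient trajectories "to examine patterns in recovery for the key variables of quality of life and lung health" and adds: "Mean trajectories will be used to summarize the typical trajectory". It plans latent class analysis for recovery groups, and multivariable regressions of baseline and severity variables to see "how these impact outcomes at 3, 6, 12, 18, and 24 months after ICU discharge". On missing data it covers drop-out and item-missing values, and says "we may use multiple imputation methods as a sensitivity analysis to compensate for missing data". Tests that stop because the patient has recovered are not mentioned there. The Limitations section promises a correction for drop-out, which is a different matter.

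**The concern.** Under the text rule, whether a later value exists depends on the outcome itself. At 3 months everyone who attends is tested. At each later visit a patient is tested only if the previous result was abnormal. Recovered patients leave the average and slower recoverers stay in it, so the average at a late visit no longer describes the typical patient.

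Lung health is one of two variables that the plan names as key. A mean curve or a 24-month regression built from recorded spirometry or walk distance would describe a selected group that shrinks at each visit, and could be reported as persistent impairment of the whole cohort.

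The footnote adds a data-collection problem. Read literally, it has tests repeated when they become normal, whereas the text has them stopped. Sites that follow different places in the article would collect different data.

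**Working it through.** The plan gives no mean, standard deviation, recovery rate or normal limit for any lung test, so it has no figure of its own to reproduce on this point. The sample-size statement does not enter.

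**From the article:** visits at 3, 6, 12, 18 and 24 months; a test is dropped after the first normal result.

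**Assumed:** a percent-predicted scale, normal at 80 or above, visit error SD 4, no deaths or drop-out. The mean at month t is m + g × (1 − exp(−(t − 3)/6)), where m is the 3-month mean and g the recovery parameter. Each scenario simulates 200,000 patients.

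**Base scenario** (m = 75, g = 8, between-patient SD 15, the same recovery in every patient):

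| Month | 3 | 6 | 12 | 18 | 24 |
|---|---|---|---|---|---|
| Mean if all were tested | 75.0 | 78.1 | 81.2 | 82.3 | 82.7 |
| Mean of recorded values | 75.0 | 69.4 | 70.0 | 69.1 | 68.2 |
| Still tested | 100% | 63% | 52% | 44% | 39% |

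The cohort gains 82.7 − 75.0 = 7.7 points, while the recorded mean loses 75.0 − 68.2 = 6.8. The gap at 24 months is 82.7 − 68.2 = 14.5. It arises because the 61% no longer tested would average about (82.7 − 0.39 × 68.2)/0.61 = 92.

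Carrying the last value forward gives 80.4 at 24 months, still 2.3 too low. Regression on each patient's earlier results, which assumes data missing at random, gives 82.8 and so recovers the mean.

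**Nine scenarios at 24 months:**

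| m | g | Between-patient SD | SD of recovery | All tested | Recorded | Difference |
|---|---|---|---|---|---|---|
| 75 | 8 | 15 | 0 | 82.7 | 68.2 | −14.5 |
| 75 | 8 | 15 | 5 | 82.8 | 67.5 | −15.3 |
| 75 | 4 | 15 | 4 | 78.9 | 65.6 | −13.3 |
| 70 | 10 | 12 | 5 | 79.7 | 68.9 | −10.8 |
| 80 | 5 | 15 | 4 | 84.9 | 67.8 | −17.1 |
| 70 | 15 | 10 | 5 | 84.6 | 72.7 | −11.9 |
| 65 | 15 | 10 | 5 | 79.6 | 70.9 | −8.7 |
| 75 | 10 | 8 | 3 | 84.7 | 74.5 | −10.2 |
| 85 | 5 | 15 | 4 | 89.9 | 69.1 | −20.8 |

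The recorded mean is too low in all nine. It falls between 3 and 24 months in seven. In the other two it still rises, but by less than the cohort (65.0 to 70.9 against 79.6, and 70.0 to 72.7 against 84.6). A wider set of 30 assumed scenarios, not itemised here, gave shortfalls of about 6 to 26 points, always in the same direction.

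**Percentages.** Take a 3-month mean of 75, SD 14, a mean gain of 10 by 24 months and within-patient SD 5. Then 38% are truly abnormal at 24 months, 33% are still tested, and 88% of those tested are abnormal. Using the tested as denominator overstates abnormality (88%). Using everyone, with previously normal patients counted as normal, gives 0.33 × 0.88 = 29%, which understates it. Neither is the current prevalence.

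**The case against.** The strongest reply is that the article does not fix an estimator. Mean trajectories need not be raw averages at each visit, and a condensed article may leave the model to an analysis plan that is not shown. A model using all earlier results recovered the true mean above. This stands in part: the bias is conditional on using recorded values alone. The stopping rule and the mean and per-visit analyses are nevertheless both stated, and nothing stated connects them. How an untested visit is coded also has to be settled while data are being collected.

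Several stronger readings are tempting, and the documents do not support them:

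- *All lung and quality-of-life results are biased.* The SGRQ, SF-36, PHQ-9, MoCA and blood analysis carry no dagger and continue at all five visits. Lung health is not tied to a measure, so an SGRQ trajectory would be sound.
- *Later means describe only abnormal patients.* Each later visit includes patients who become normal at that visit. The selection is on the previous result.
- *The curve will show decline.* It did in seven of nine scenarios, not in all.
- *The fast and slow recovery classes are biased.* This was not tested, and a latent class mixed model could be part of the remedy.
- *Sites will stop at different limits.* The article gives no limit, but ranges may stand in the full protocol or case report form. A single numerical limit for each test is not a reasonable demand either, since a chest x-ray has none.
- *Relapse will go unseen.* That is true of the stopped tests only. Respiratory-failure admissions, new respiratory infections and the SGRQ are still recorded.

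The footnote may be a slip of one word. It still contradicts the text as printed.

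**Conclusion.** The point holds in conditional form. If the mean trajectories and per-visit regressions of lung health use only recorded values of the stopped tests, they understate recovery from 6 months on and may show decline while the cohort improves. The 3-month mean is not affected.

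The direction was the same in every scenario tried. The size, about 6 to 26 percent-predicted points at 24 months, rests wholly on assumed values, because the documents give nothing to fix it.

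The contradiction between the Table 1 footnote and Pulmonary Assessment needs no assumption. Which testing schedule is right is not judged here.

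This should be fixed. It does not undermine the study as a whole: the study is descriptive, several key measures lie outside the rule, and the remedy is available from data already planned.

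**What to change.** 1. In Statistical Considerations, state that continuous tests under the stopping rule are not summarised by per-visit means or regressions of recorded values alone. Use a likelihood-based mixed model, or a latent class mixed model, on all visits, including the normal value that triggered stopping. Add interval-censored time to first normal result for every stopped test, chest x-ray included.
2. In the case report form, code a test not done because previously normal separately from a missed test, and record the result and the reference range used for the decision. Report the percentage never yet normal among patients alive and in follow-up under that label. It must not be presented as the current prevalence of abnormality, which it understates.
3. Reconcile the Table 1 footnote with Pulmonary Assessment.
4. If the stopping rule stays, state that relapse on the stopped tests cannot be estimated from those tests.

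The cost is analysis wording, a few form fields and one footnote. The downside is that the mixed model assumes data missing at random. That requires stopping to depend on recorded values, which is why the result and range behind each decision must be captured; it also requires later unobserved values to follow the modelled recovery.

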#### Assessment of Health-Related Quality of Life

The Short Form Health Survey, a patient-reported questionnaire consisting of 36 items, will be used to assess health-related quality of life (24, 25). Symptoms suggestive of depression will be screened through the Patient Health Questionnaire-9, a self-administered diagnostic instrument which has been validated for use as a screening tool in primary care (26). Additionally, we will assess whether the patient was able to return to work and under what conditions, which is an important economic and well-being outcome.

At the 3 month post-ICU discharge follow-up visit, we will determine the patient's clinical frailty score before ICU admission, through recollection of his/her clinical status by the patient and/or relatives. The used score ranges from 1 (very fit) to 9 (terminally ill) (27).

#### Assessment of the Dynamics of Kidney, Cardiac, Liver, and Neurological Injury and Recovery

Any hospital admission for neurological decompensation, cardiac, renal or liver failure since ICU discharge or last follow-up visit will be recorded, as well as the need for hemodialysis in case of renal failure. Liver, heart and renal biomarkers (e.g., creatinine, estimated glomerular filtration rate, liver function tests, brain-natriuretic peptide) and full blood count will be determined in a blood sample at every follow-up visit. Potential cognitive impairment will be screened through the Montreal cognitive assessment (28). In patients who underwent an echocardiography during their ICU stay, a follow-up focussed echocardiography will be performed at 3, 12, and 24 months or until normalization.

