## Discussion

This study aims to provide a comprehensive understanding of the long-term impact of COVID-19 in patients who have been admitted to ICU. The primary outcome of the study is to extensively characterize physical, mental and psychosocial consequences post ICU discharge. Secondary outcomes include long-term health and social-economic cost of COVID-19, risks for medical sequelae and long-term survival.

The emerging data and evidence suggest that a significant proportion of critically ill COVID-19 patients will present persistent debilitating symptoms, organ dysfunctions and compromised quality of life post-hospital discharge (4, 6, 12). Results obtained from this study will assist clinicians and healthcare providers to better identify high risk patients who are recovering from COVID-19, then to target interventions that improve their post-COVID-19 quality of life, facilitating a quicker return to productive life. Better understanding of the long-term impact of COVID-19 through data collected in this study will help and inform governments and policy-makers to better allocate resources.

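### As described, follow-up admissions are recorded by listed cause, which does not fit secondary outcomes of health and socio-economic cost and medical sequelae

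*Protocol article*

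**What the plan says.** Two sections of the protocol article describe which admissions are recorded during follow-up.

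- Pulmonary Assessment: "Any admission for respiratory failure or a new respiratory infection since ICU discharge or last follow-up visit will be recorded".
- Assessment of the Dynamics of Kidney, Cardiac, Liver, and Neurological Injury and Recovery has the matching rule for the other organs: "Any hospital admission for neurological decompensation, cardiac, renal or liver failure since ICU discharge or last follow-up visit will be recorded". The same sentence also covers dialysis: "as well as the need for hemodialysis in case of renal failure".

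The only other follow-up item with a clear economic content is in Assessment of Health-Related Quality of Life: "we will assess whether the patient was able to return to work and under what conditions, which is an important economic and well-being outcome".

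The outcomes are named in the Discussion. After a primary outcome of characterizing physical, mental and psychosocial consequences, it says: "Secondary outcomes include long-term health and social-economic cost of COVID-19, risks for medical sequelae and long-term survival". Readmission is not itself a named outcome. It appears only as background in the Introduction, which cites reports that "at least 10% of all hospitalized COVID-19 survivors have been readmitted within 2 months" and that survivors "presented a 33% increase in risk of developing new psychiatric or neurological diseases within the first 3 months".

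**The concern.** A cost outcome needs hospital use whatever its cause, because a bed-day costs the same kind of resource whether the reason is heart failure or a gastrointestinal bleed. The article names such an outcome but describes a recording rule that selects admissions by cause. The same applies to those medical sequelae that show themselves as events leading to admission, such as a later embolism or infarction.

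The filter acts at the site, before anything is entered. An admission judged to lie outside the list leaves no record, so it cannot be reclassified centrally later. With 14 centers in 11 countries and more being recruited, sites may draw the line differently, and recorded admission rates could differ between them for similar patients.

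**Working it through.** The article gives no figure for readmission in its own cohort, for cost, or for the share of admissions by cause, so there is no planned figure to reproduce. The check is a comparison of sections, followed by the direction of the error.

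**1. Coverage.** The left column takes conditions from the article's list of ICU complications, plus psychiatric disease from the Introduction. The right column asks whether a later admission for that condition falls under the two recording rules.

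| Reason for a later admission | Covered as described? |
|---|---|
| Bacterial or viral pneumonia | Yes, if a new respiratory infection |
| Stroke, seizure | Probably, as neurological decompensation |
| Congestive heart failure, acute renal failure | Yes |
| Pulmonary embolism, deep vein thrombosis | Only if the site classes it as respiratory or cardiac failure |
| Myocardial infarction | Only if classed as cardiac failure |
| Gastrointestinal hemorrhage | No |
| Bacteremia or sepsis from a non-respiratory source | No |
| Pancreatitis | No |
| Psychiatric illness | No |

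No section of the article describes recording admissions for any cause.

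**2. Direction.** Let C be the true hospital-use cost and s the share of it that arises from listed-cause admissions, with s between 0 and 1. If only listed-cause admissions are entered, the recorded cost is s × C and the relative error is (s × C − C) / C = s − 1. This is zero when s = 1 and negative otherwise. Apart from sites entering unlisted admissions under a listed cause, the error can only be downward.

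**3. Size.** The documents do not give s. The following is purely an illustration in terms of patients readmitted. It assumes that the background rate of 10% applies to the target enrolment of 1,000, so 1,000 × 0.10 = 100 patients, each readmitted once.

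| Assumed share under listed causes | Recorded | Missed |
|---|---|---|
| 30% | 100 × 0.3 = 30 | 70 |
| 50% | 100 × 0.5 = 50 | 50 |
| 70% | 100 × 0.7 = 70 | 30 |
| 90% | 100 × 0.9 = 90 | 10 |

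The range is wide because every share in it is assumed. The 10% is also a 2-month figure (a lower bound) for all hospitalized survivors, whereas this study follows ICU survivors for 24 months. The table shows how strongly the result depends on s. It is not an estimate.

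**4. What is unaffected.** Table 1 schedules the SF-36, PHQ-9, SGRQ, MoCA and blood analysis at all five visits, and lung function until it normalizes. These measure sequelae directly and do not depend on which admissions are recorded.

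**The case against.** The strongest reply is that neither sentence excludes other admissions. Each opens an organ-specific section and names the events relevant to that organ. The article condenses a fuller protocol and points to a detailed case report form on the study website, which may hold a general readmission field. Table 1 is visibly not a full field list either, since return to work is not in it. This stands: that sites collect only listed-cause admissions is an inference, and the point has to be conditional on the form following the text.

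A reader might go further and infer that the study will undercount its readmission rate, for example that a true 10% would appear as 5% to 7%. The documents do not support that. All-cause readmission is not a declared outcome, and those figures need an assumed 30% to 50% of admissions outside the list. A reader might also infer that the risk of sequelae cannot be estimated at all. That is not so either, because most sequelae are measured at the visits, and depressive symptoms are screened by the PHQ-9 at each of them.

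Two further replies are fair. The article does not say how cost is computed, or that it is built from these admissions, and a costing method may properly be left to a fuller document. The list of ICU complications describes the acute stay and sets no standard for follow-up; here it serves only as a source of plausible reasons for readmission.

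What remains is that the article did choose to say which admissions are recorded, twice, and both times by cause. Besides dialysis and return to work, it describes no other cost-related follow-up item. Organ-specific capture suits the aim of studying organ injury and recovery, but it does not suit a cost outcome.

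**Conclusion.** The described recording of admissions does not fit the stated secondary outcomes. If the case report form follows the article, admissions for unlisted causes would be missed, and a cost based on hospital use would be too low. Sequelae that come to light only through such admissions would also be incompletely counted; those measured at visits would not be affected.

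The size is unknown. It depends on the share of hospital use under the listed causes, which the documents do not give. The conclusion rests on two assumptions: that the form is no broader than the text, and that hospital admissions enter the cost outcome. If the form already records all admissions, only the article's wording needs correction. This should be resolved, but it concerns secondary outcomes and does not touch the primary characterization of recovery through the scheduled assessments.

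**What to change.** In Pulmonary Assessment and in the section on kidney, cardiac, liver and neurological injury, replace the cause-limited sentences with one rule: at each visit, record every hospital admission since ICU discharge or the last visit, with date, length of stay and main cause. Derive the respiratory, neurological, cardiac, renal and liver admissions from that list, so that nothing now planned is lost.

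If all-cause recording is not feasible, narrow the secondary outcome in the Discussion to listed-cause admissions and return to work.

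The cost is slightly more data entry at visits where admissions are already asked about. Sites would still assign the cause, so organ-specific counts could still vary between them; the all-cause total would not depend on that judgement, and the recorded cause could be reviewed centrally. Enrolment began in January 2021, so if the form is currently restricted, earlier admissions of patients already in follow-up would have to be recovered by recall or record review. That favors an early change.
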